**Methods:**

This German study consists of a low-threshold online screening for PACS where positively screened participants will be supported throughout by personal pilots. The personal pilots are aimed at empowering patients and helping them to navigate through the study and different treatment options. Patients will then be randomly assigned either to an intervention group (IG) or an active control group (ACG). The IG will receive a comprehensive assessment of physiological and psychological functioning to inform future treatment. The ACG does not receive the assessment but both groups will receive a treatment consisting of an individual digital treatment program (digital intervention platform and an intervention via a chatbot). This digital intervention is based on the needs identified during the assessment for participants in the IG. Compared to that, the ACG will receive a more common digital treatment program aiming to reduce PACS symptoms. Importantly, a third comparison group (CompG) will be recruited that does not receive any treatment. A propensity score matching will take place, ensuring comparability between the participants. Primary endpoints of the study are symptom reduction and return to work. Secondary outcomes comprise, for example, social participation and activities in daily life. Furthermore, the feasibility and applicability of the online screening tool, the holistic assessment, digital trainings, and personal pilots will be evaluated.

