### Study sample and recruitment

Inclusion and exclusion criteria for the current study are summarized in Table 1.

**Table 1 Tab1:** Eligibility criteria

Inclusion criteria	Exclusion criteria
Patients perceive PACS symptoms	High need for care as classified according to German health care levels (>/= 2)
Patients who have the necessary prerequisites to participate in the online-screening as well as in telephone or video-conferences with their personal pilots	No mobile device (smartphone, laptop, tablet, or computer) and/or internet connection, no telephone or video conference system, or no sufficient technology literacy to make use of it
Registered in Bavaria, Germany	Occupancy in the healthcare or welfare system or laboratory
Age between 18 and 60 years	PACS treatment or therapy (including rehabilitation)
Willingness to participate in outpatient or (partially) inpatient therapy	Acute COVID-19 infection less than 4 weeks ago
Sufficient German skills	Insufficient literacy of the German language to participate in data collection and digital treatment options Severely limited cognitive, hearing and vision abilities, as linguistic components of the digital offers and auditory stimuli must be understood
Physical conditions that allow participants to take part in the digital intervention exercises	Severely limited physical conditions such as bedriddenness
Patients that do not receive PACS treatment so far	

Patients will be asked to participate in the study after they were positively screened in the initial online screening. The *recruitment* will be carried out in two ways: Firstly, patients are sought to be reached via multiplicators. These include general practitioners (GPs) and specialized primary care physicians, post-COVID outpatient clinics and administrative institutions. GPs and specialists will be informed in advance about the possibility of the screening based on an existing address database. It is assumed that approximately every tenth physician will identify patients as potential candidates and can refer approximately one patient to the study. If 1000 multiplicators are contacted, about 100 potential participants can be screened.

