#### 1. Low-threshold online screening tool

To establish a quick and easy-to-use screening tool for patients who assume that their symptoms are due to PACS, a low-threshold online screening instrument was developed and will be evaluated during the duration of the project (see Additional file 1﻿: Appendix). The screening is of subjective nature. It consists of 14 questions that assess symptoms related to PACS. In addition, the screening includes further questions that assess the diagnosis and timeline of acute COVID-19, limitations in daily life and previous treatment measures to reflect the inclusion and exclusion criteria. Furthermore, demographic questions are asked about age, sex, and place of residence.

If the responses indicate the likelihood of PACS, and that the participants meet the inclusion criteria (Table 1), participants are asked to provide their contact details so that they can be contacted by the personal pilot and take part in the study. In this case, patients are randomly assigned to either the intervention group (IG) or the active control group (ACG). If a randomized approach is not possible (e.g., if it is not possible for a patient to take part in the three-day assessment program), they will not be randomly assigned but marked for the statistical analyses. If there is no indication of a PACS in the screening tool, participants will be directly informed of this, and advised to contact their GP for further clarification and support. In the scope of the project, the online screening will be validated with the results of the assessment program to ensure that the screening can reliably identify patients suffering from PACS and inform future interventions. In detail, the results from the assessment will serve as a gold standard for the validation of the online screening. That is, after the assessment, practitioners will be asked to decide to what extent patients are indeed affected by PACS. This decision will be used to be able to determine the sensitivity for the online screening. In case of an acceptable match between the decision of the practitioners and the online screening, the online screening can be used as a starting point for appropriate treatment of patients and Hypothesis 1 that a short screening is able to detect the presence of PACS will be validated.

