#### 2. Comprehensive assessment program (intervention group only)

After the randomization and an initial interview with the personal pilot, patients in the IG are assigned to a 3-day inpatient assessment. During the assessment, the functional capacity will be examined by different disciplines according to the bio-psycho-social model of the International Classification of Functioning (ICF) (DIMDI, 2005) and the need for treatment will be identified depending on the debilitating symptoms.

The 3-day inpatient assessment takes place in a specialized clinic (neurological-orthopedic stationary rehabilitation center). This clinic has the necessary (specialist) competence in the fields of neurology and orthopedics including physiotherapy, internal medicine, and psychology. The assessment aims to check in more detail and on basis of objective tests for the presence of PACS. Furthermore, the goal is to determine an individual interdisciplinary and cross-sectoral treatment plan, which can be translated into practice. This plan is then guided by the personal pilot in terms of empowering the patients to know about their symptoms, the recommended treatments, and what they can do themselves also by means of the digital training.

Concretely, the assessment is performed by means of physiological and psychological tests (see Table 2). These tests are based on the recommendations of the S1-guidelines (e.g., [17]) and consist also of a detailed medical history and review. From this, further individual assessments are derived adaptively. They are carried out by different therapists from the professional groups of pneumology, cardiology, internist, psychology, neurology, physiotherapy, occupational therapy, and nursing.

**Table 2 Tab2:** Diagnostic tools within the assessment

Domain	Parameter/ tests
Physical conditions and vital signs	• Height • Weight • Body fat • Pulse • Electrocardiography at rest • Oxygen saturation • Body temperature • Blood pressure • Breathing frequency
Lung	• Spirometry
Brain	• EEG • Initial neurological examination
Nerves	• Nerve conduction velocity • Somatosensory evoked potentials (SEP)
Stress test	• Schellong orthostasis test • Ergometry
Taste/smell	• Taste/smell tests (SS-16)
Psychological	• Attention test battery • Alertness test • California Verbal Learning test • Five Point test (divergent thinking) • Visual scanning test • Working memory test
Ability-to-act investigation	• Occupational therapy

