#### Type of statistical analysis used

To test the aforementioned hypotheses, first, a propensity score matching will be applied between the IG and the CompG. Sensitivity analyses and test–retest reliabilities will be used to test Hypothesis 1 and 2 respectively. To test Hypothesis 3, MANOVA and repeated measurement ANOVAs will be used. To assess Hypothesis 4, no statistical analyses but a qualitative approach will be used. For the last hypothesis (Hypothesis 5), repeated measurement ANOVAs and MANOVAs will be used.

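### Sensitivity of the online screening cannot be estimated, because only screen-positive patients in the intervention group receive the reference assessment

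*Protocol article*

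**What the plan says.** The section on the low-threshold online screening tool makes the clinic assessment the reference standard: "the results from the assessment will serve as a gold standard for the validation of the online screening". After the assessment, practitioners judge how far each patient is affected by PACS, and the section continues: "This decision will be used to be able to determine the sensitivity for the online screening". If that judgement and the screening agree acceptably, the tool may serve as the entry point to treatment and Hypothesis 1 is taken as validated.

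Other statements fix who is assessed:

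- Study sample and recruitment: "Patients will be asked to participate in the study after they were positively screened in the initial online screening".
- Online screening tool: "If there is no indication of a PACS in the screening tool, participants will be directly informed of this, and advised to contact their GP".
- Section 2 on the comprehensive assessment program: its heading limits the assessment to the intervention group (IG).
- Abstract, Methods, on the active control group (ACG): "The ACG does not receive the assessment".

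The section Type of statistical analysis used adds only this: "Sensitivity analyses and test–retest reliabilities will be used to test Hypothesis 1 and 2 respectively". Read with the screening section, the first term must mean diagnostic sensitivity, not robustness analyses.

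**The concern.** Sensitivity is the share of people with PACS whom the tool flags. Estimating it requires knowing how many people with PACS the tool fails to flag, so some people with a negative screen must receive the reference assessment. Under this plan none do. The measure named for Hypothesis 1 and the group that is assessed are therefore incompatible.

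The claim matters beyond this trial. The Research Project section lists dissemination of validated instruments, with the screening as its example, among the long-term goals. The Discussion says the screening should find as many probable cases as it can. Both depend on missed cases, about which the planned data say nothing. People with a negative result are also told so directly, which makes the false-negative rate the error that users most need to know. A positive finding on Hypothesis 1 could be published as evidence of detection although no missed case could have appeared in the data.

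**Working it through.** The article gives no figure for screening accuracy and no validation sample size, so there is none to reproduce. The check rests on the two-by-two table and on the precision of what remains estimable.

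**Step 1: which cells are observed.**

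| | Clinician: PACS | Clinician: no PACS |
|---|---|---|
| Screen positive, assessed in IG | TP | FP |
| Screen negative | FN, never assessed | TN, never assessed |

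- Sensitivity = TP/(TP + FN). FN is unobserved, so the assessed data contain none and the formula returns TP/(TP + 0) = 100%.
- Specificity = TN/(TN + FP). TN is unobserved, so it cannot be estimated.
- PPV = TP/(TP + FP). Both cells are observed, so it can be estimated.

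**Step 2: the same data fit very different tools.** Assume 66 assessed patients (the IG size in Sample size planning) and a PPV of 0.80, which the documents do not give. Expected confirmations are 0.80 × 66 = 52.8, about 53. For a prevalence p among people screened (also an assumption), the specificity that produces this PPV is

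Sp = 1 − [p × Se × (1 − PPV)/PPV]/(1 − p).

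At p = 0.50 this reduces to Sp = 1 − 0.25 × Se:

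| True sensitivity | Matching specificity | Expected confirmed of 66 | Missed per 100 people with PACS |
|---|---|---|---|
| 0.30 | 0.925 | 53 | 70 |
| 0.60 | 0.850 | 53 | 40 |
| 0.90 | 0.775 | 53 | 10 |
| 0.95 | 0.763 | 53 | 5 |
| 0.99 | 0.753 | 53 | 1 |

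At p = 0.80 the formula becomes Sp = 1 − Se, and the same 53 of 66 is expected at a sensitivity of 0.30 (specificity 0.70) or 0.90 (specificity 0.10). The assessed data cannot separate these cases. Counting everyone who takes the screening does not help: the share screening positive multiplied by the PPV gives p × Se, but p is unknown.

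**Step 3: precision of the PPV.** The normal-approximation half-width is 1.96 × √[PPV × (1 − PPV)/n].

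- n = 66: 1.96 × √(0.80 × 0.20/66) = 0.097.
- n = 44: 1.96 × √(0.80 × 0.20/44) = 0.118. The Evaluation concept section assigns a roll of 1 or 2 to the IG, so 132 × 2/6 = 44.

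Exact 95% intervals with 66 assessed:

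- 46/66 = 0.70 (0.57 to 0.80)
- 53/66 = 0.80 (0.69 to 0.89)
- 59/66 = 0.89 (0.79 to 0.96)

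**Step 4: what a sensitivity estimate would need.** With everyone assessed regardless of screening result, the number of people with confirmed PACS is 1.96² × Se × (1 − Se)/h² for half-width h, rounded up. Both sensitivities are assumed.

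| Assumed sensitivity | h = 10 points | h = 5 points |
|---|---|---|
| 0.80 | 62 | 246 |
| 0.90 | 35 | 139 |

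**The case against.** The strongest reply is that the article never commits to computing TP/(TP + 0). Its decision rule is acceptable agreement between clinician and screening, and that rule can fail: if clinicians reject many positive screens, agreement is poor. On this reading the authors would report a confirmation rate under the wrong name. That is fair as to what they would probably compute, but the confirmation rate is the PPV. It does not support a claim about sensitivity or about detecting PACS in people who take the screening.

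A second reply is that PPV is not all the data offer. The clinician's judgement is graded and the tool has 14 symptom questions, so their association can be studied within assessed patients. This stands as a useful supplement, but it gives no sensitivity at the entry cut-off.

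Third, the assessed patients are also filtered by the eligibility criteria and by ability to attend the clinic. This is correct, and the replacement measure should say so.

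Fourth, the primary endpoints are symptom reduction and return to work, and the sample size serves the IG–ACG comparison. This limits the reach of the problem to Hypothesis 1. Within that hypothesis, a larger sample or better modelling under the same design would not repair it.

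Finally, Fig. 3 and Additional file 1 are not shown. The text nevertheless sends people with a negative screen to their GP and mentions no route to the clinic. Nor is this a detail left to an SAP, because the article itself fixes both the measure and the assessed group.

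**Conclusion.** The concern holds. Sensitivity and specificity of the screening are not estimable under the plan as written, and a sensitivity computed from the assessed patients would be 100% by construction. This follows from the design alone and needs no numerical assumption. Tools that miss 5 or 40 of every 100 people with PACS can produce the same assessed data, given compensating specificity.

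The estimable quantity is the PPV among eligible, assessed IG patients. Its 95% half-width is about 10 points at n = 66 and about 12 points at n = 44, both at an assumed PPV of 80%. The 50% and 80% prevalences are also assumptions and serve only as illustration.

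The text on Hypothesis 1 must be corrected before analysis, because following it would yield an invalid validation claim. The primary IG–ACG comparison is not affected.

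**What to change.** - In the online screening section and in Type of statistical analysis used, replace sensitivity with the positive predictive value among eligible screen-positive IG patients who complete the assessment, with a 95% confidence interval.
- Restrict Hypothesis 1, in The Research Project and in the screening section, to the claim that most positive screens are confirmed by the clinician.
- State that sensitivity and specificity are not estimable, because nobody with a negative screen is assessed.
- Optionally, report the relation between the screening symptom score and the clinician's graded rating within assessed patients, labelled as such.

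The cost is a change of wording and a narrower claim, with no new procedures. If the sponsor wishes to keep the sensitivity claim, people with a negative screen, either all of them or a random sample with weighting for selection, would have to receive the reference assessment. That is a change of design, and the numbers in step 4 of the working show its scale when everyone is assessed.

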#### 2. Comprehensive assessment program (intervention group only)

After the randomization and an initial interview with the personal pilot, patients in the IG are assigned to a 3-day inpatient assessment. During the assessment, the functional capacity will be examined by different disciplines according to the bio-psycho-social model of the International Classification of Functioning (ICF) (DIMDI, 2005) and the need for treatment will be identified depending on the debilitating symptoms.

The 3-day inpatient assessment takes place in a specialized clinic (neurological-orthopedic stationary rehabilitation center). This clinic has the necessary (specialist) competence in the fields of neurology and orthopedics including physiotherapy, internal medicine, and psychology. The assessment aims to check in more detail and on basis of objective tests for the presence of PACS. Furthermore, the goal is to determine an individual interdisciplinary and cross-sectoral treatment plan, which can be translated into practice. This plan is then guided by the personal pilot in terms of empowering the patients to know about their symptoms, the recommended treatments, and what they can do themselves also by means of the digital training.

Concretely, the assessment is performed by means of physiological and psychological tests (see Table 2). These tests are based on the recommendations of the S1-guidelines (e.g., [17]) and consist also of a detailed medical history and review. From this, further individual assessments are derived adaptively. They are carried out by different therapists from the professional groups of pneumology, cardiology, internist, psychology, neurology, physiotherapy, occupational therapy, and nursing.

**Table 2 Tab2:** Diagnostic tools within the assessment

Domain	Parameter/ tests
Physical conditions and vital signs	• Height • Weight • Body fat • Pulse • Electrocardiography at rest • Oxygen saturation • Body temperature • Blood pressure • Breathing frequency
Lung	• Spirometry
Brain	• EEG • Initial neurological examination
Nerves	• Nerve conduction velocity • Somatosensory evoked potentials (SEP)
Stress test	• Schellong orthostasis test • Ergometry
Taste/smell	• Taste/smell tests (SS-16)
Psychological	• Attention test battery • Alertness test • California Verbal Learning test • Five Point test (divergent thinking) • Visual scanning test • Working memory test
Ability-to-act investigation	• Occupational therapy
Internal diagnostics	• Echography • Carotis-duplex sonography

The results of the assessment for each professional group will be handed to a clinician, who is then able to make a holistic assessment of whether PACS is present or not. These assessments are also summarized to form a holistic treatment plan, which synopsizes the findings and lists the indicated medical and therapeutic measures. These recommendations will be made visible for the personal pilot, and subsequently made available to the attending outpatient doctor.

The prescription of necessary treatments and aids, as well as the recommendation of digital interventions already take place within the framework of discharge management. If the need for a rehabilitation measure is determined, this will be communicated to the patient directly in a way to enable him/her applying for rehabilitation treatment and finding the most appropriate treatment within Germany (also with the help of the personal pilot).

Using such an approach allows us to test Hypothesis 2, that a comprehensive assessment can determine rehabilitation or remedial needs and the leading rehabilitation indication. To assess the applicability of this hypothesis, we will consider a comparison of test–retest reliabilities of the degree of experienced symptoms in the IG compared with the ACG and the CompG. Furthermore, the assessment allows us also to test Hypothesis 5 that an interdisciplinary treatment pathway empowers the patient. To assess the applicability of this hypothesis we will check whether IG, ACG and CompG differ in terms of the development of symptoms, increased activities of daily lives, RTW and increased social participation. To do so, we will consider MANOVA and repeated measurement ANOVA analyses.

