### The Research Project

The objective of the present study is the early detection of post-acute COVID-19 symptoms (PACS) and subsequently a long-term and sustainable holistic care and support of patients with PACS to avoid long-term illness and chronification, and to enable social participation.

The long-term goals of the study are the dissemination of validated instruments (i.e.g., the online screening) and newly developed treatment approaches (i.e., the digital interventions and a  personal pilot concept) through communication to central stakeholders such as medical associations, health insurance companies, service providers in the outpatient and inpatient sector as well as professional societies and care institutions. In this way, patient care is to be improved beyond the project duration and care services are to be made more efficient.

Hypotheses, which will be tested with this project, are the following:A short *screening* can detect the presence of PACS.A comprehensive* assessment* can validly and reliably determine rehabilitation or remedial needs and the leading rehabilitation indication and be basis of an individual multidisciplinary treatment plan.The more *individualization* the digital therapy offers, the higher the effectiveness in the treatment of PACS.As contact point for all involved parties, a *personal pilot * empowering the patient suffering from PACS can -by means of an interdisciplinary and intersectoral treatment planning- ensure the sustainable management of interdisciplinary treatment.An *interdisciplinary treatment pathway* and the personal pilots empower the patients, so that the patients receive the appropriate diagnosis and treatment, and to actively participate in their own recovery, ensuring patients recover quickly and sustainably from their PACS conditions, increase their functional capacity, reduce incapacity to work and regain participation.

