### Evaluation concept

A longitudinal randomized control trial design is used in this project with a three-group pretest–posttest procedure. Whereas the CompG will be recruited with different links via online invitations (e.g., via social media campaigns), the IG and the ACG are recruited with another separate link. After agreeing to take part in the study, participants will be randomized by throwing a dice. Patients for whom a 1 or 2 was rolled are placed in the IG and patients for whom a 3–6 was rolled are placed in the ACG. If a randomization cannot be realized (e.g., because they cannot take part in the stationary assessment due to organizational limitations), patients will be allocated to the ACG but will be marked for statistical analyses. Methodically, a propensity score matching will be used between the IG and the CompG to ensure the comparability of these groups (i.e., participants will statistically be matched by various person-related criteria such as age and sex). All groups are repeatedly interviewed with similar instruments in each group (see Table 1). Time points of measurement are the screening (T1), prior to the assessment in the IG and a comparable time point in the ACG (T2), after the assessment in the IG and at a comparable time point in the ACG (T3). Then approximately 6 weeks after T3 and after symptom-specific digital interventions, a further measurement will take place (T4). Another 6 weeks later a follow-up measurement will take place (T5). A last measurement time point (T6) will be conducted 6 months later with some selected participants. All time points of measurement are included in the study flow chart (Fig. 3).

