For the *summative effectiveness evaluation*, the primary endpoint is the symptom reduction regarding PACS, and RTW. Secondary outcomes include social participation, health-promoting behaviors, and activities of daily living (ADL) as well as mental health and life satisfaction/quality of life. Survey and documentation of all endpoints are conducted by means of questionnaires and/or interviews with study participants who have completed interventions over the course of the project as described above. In addition, possible moderators (especially socio-demographic data) and mediators (e.g., motivation, self-efficacy, and coping strategies) are quantitatively reviewed and added to the analyses. An overview of the measures is provided in Table 2 and Additional file 1.

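### The planned test of Hypothesis 2 compares the stability of symptom reports between arms, so it cannot show that the clinic assessment is valid or reliable

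*Protocol article*

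**What the plan says.** In *The Research Project*, the protocol article states Hypothesis 2: a comprehensive assessment "can validly and reliably determine rehabilitation or remedial needs and the leading rehabilitation indication", and can form the basis of an individual treatment plan.

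The test is given twice. The section on the assessment program says that the hypothesis will be judged by comparing test-retest "reliabilities of the degree of experienced symptoms in the IG compared with the ACG and the CompG". *Type of statistical analysis used* pairs sensitivity analyses and test-retest methods with the first two hypotheses: "reliabilities will be used to test Hypothesis 1 and 2 respectively". The second of each pair belongs to Hypothesis 2, and no other test of it is named.

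The assessment section is headed "Comprehensive assessment program (intervention group only"). Its findings go to one clinician, "who is then able to make a holistic assessment of whether PACS is present or not", and are summarised into a treatment plan. *Evaluation concept* places the assessment between T2 and T3, the latter being "after the assessment in the IG and at a comparable time point in the ACG (T3"). No repeat is described. The same section says that "the primary endpoint is the symptom reduction regarding PACS, and RTW".

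**The concern.** The hypothesis is about a clinical determination: does this work-up identify who needs rehabilitation, and for what? The statistic is about something else, namely whether patients give similar symptom ratings on two occasions. Two of the three groups in the comparison never have the assessment, so they offer nothing whose reliability could be set against the IG's.

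There is a second difficulty. Test-retest reliability presumes a stable state, while the trial sets out to change symptoms and, under Hypotheses 3 and 5, looks for differences between arms in how symptoms develop. The same change could be an effect under those hypotheses and appear as unreliability under Hypothesis 2.

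At stake is a published statement that the assessment has been shown to be valid and reliable, resting on a number that cannot bear on it. This matters beyond Hypothesis 2, because *Low-threshold online screening tool* takes the assessment as the gold standard for the screening under Hypothesis 1.

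**Working it through.** **Step 1: match the test to the hypothesis.**

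| Needed for Hypothesis 2 | What the article provides |
|---|---|
| A measure of rehabilitation need or leading indication | Degree of experienced symptoms |
| Reliability: the determination made twice, or by two independent judges | One assessment, one overall judgement |
| Validity: an external criterion for rehabilitation need | None named |
| Data on the assessment in each group compared | IG only |

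No row is met. This step needs no arithmetic and carries the point.

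**Step 2: the article's own figures.** It gives no reliability figure. Its only design figure is 68% power for N = 132 (66 per arm) at alpha 0.05 and an effect of 0.15. For a within-between interaction with two time points and zero correlation, lambda = 0.15² × 132 × 2 = 5.94, which gives power 0.677, so 68% is reproduced if 0.15 is Cohen's f. Read as d between two means with 66 per arm, power is 0.136. For two groups f = 0.15 corresponds to d = 0.30. I use 0.15 and 0.30 below only as anchors for plausible change, and 0.50 as a larger case.

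**Step 3: how treatment effect can enter the statistic.** Assumptions, none from the article: baseline SD 1, true retest reliability 0.80, measurement error unchanged, and improvement independent of baseline, with mean δ and between-patient SD τ. Then the covariance is 0.80, the first variance is 1 and the second is 1 + τ².

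- r = 0.80 / √(1 + τ²)
- Agreement ICC = 0.80 / [(1 + 1 + τ²)/2 + δ²/2]
- Consistency ICC = 0.80 / [(1 + 1 + τ²)/2]

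| δ | τ | r | Agreement ICC |
|---|---|---|---|
| 0 | 0 | 0.80 | 0.80 |
| 0.15 | 0.15 | 0.80/√1.0225 = 0.79 | 0.80/1.0225 = 0.78 |
| 0.30 | 0.30 | 0.80/√1.09 = 0.77 | 0.80/1.09 = 0.73 |
| 0.50 | 0.50 | 0.80/√1.25 = 0.72 | 0.80/1.25 = 0.64 |
| 0.50 | 0 (uniform) | 0.80 | 0.80/1.125 = 0.71 |

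In the uniform case the consistency ICC also stays at 0.80. A simulation of 1,000,000 patients at δ = τ = 0.50 gave r = 0.715 and agreement ICC = 0.639, in line with the formulas.

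These are falls within one arm. The planned comparison is between arms, so a fall that the comparator shares cancels out.

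**The case against.** A reader might go further and infer that the test would penalise an effective intervention. The documents do not support that, for four reasons.

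- **Coefficient.** None is named. With uniform improvement, Pearson r and the consistency ICC do not move.
- **Direction.** The article does not say whether higher reliability in the IG would support Hypothesis 2. If lower reliability counted as support, the statistic would merely restate the treatment effect.
- **Interval.** No time points are given. T2 and T3 bracket the assessment, while the symptom-specific digital interventions come between T3 and T4. Over T2 to T3 little treatment effect would be expected.
- **Comparator.** The ACG also has a personal pilot and an individualised digital programme, so its coefficient may fall as well.

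These objections stand, and they make the confounding conditional. They do not touch the mismatch in Step 1, which holds for any coefficient, interval or direction.

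It could also be said that an article condenses the full protocol. But the article states the test in two places, so this is not detail left for elsewhere. Finally, the assessment section restates the hypothesis without the words on validity and reliability. Even in that weaker form, stability of symptom reports does not show that need has been determined.

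**Conclusion.** The concern holds in this form: the stated test of Hypothesis 2 measures the stability of symptom reports and cannot support a conclusion on the validity or reliability of the assessment. That rests on the article's text alone.

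Confounding with treatment effect is possible, not certain. Under the assumed reliability of 0.80, its size within an arm runs from negligible (r 0.79, agreement ICC 0.78) to appreciable (0.72 and 0.64) when effects vary between patients. It is nil for r and the consistency ICC when they do not vary. The difference between arms would be smaller wherever the comparator changes too.

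A reader might also infer that the main effectiveness results are compromised. They are not: symptom reduction and return to work are analysed separately from Hypothesis 2.

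**What to change.** In the assessment section and in *Type of statistical analysis used*, remove the between-arm test-retest comparison as the test of Hypothesis 2. Restate the hypothesis as a descriptive aim in the IG, for example the distribution of identified needs and leading indications with 95% confidence intervals, and make no claim that reliability or validity has been shown. If the IG reaches the planned 66, a proportion near one half has an approximate half-width of 1.96 × √(0.25/66) = 0.12.

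A cross-tabulation of leading indication against leading self-reported symptom may be added if the category mapping is prespecified, as descriptive concordance only. The assessment is meant to go beyond self-report, so low agreement could mean that it corrected the patient's account, and high agreement that it added little. Uptake of recommended measures is no substitute: the pilots' records are described as qualitative notes, and uptake depends on access.

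If questionnaire stability is of interest, report it for T1 to T2 as a property of the questionnaire, noting that pilot contact and unspecific digital content may already have begun.

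The work is rewording and a small IG-only analysis. The real cost is that the validity and reliability claim is given up. Keeping it would require data the article does not describe: a repeat or second independent overall judgement, and an external criterion for rehabilitation need.
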